### Sample size

We hypothesized that a recruitment maneuver (in HFOV modality) before surfactant administration might decrease of the need of subsequent mechanical ventilation during the first 72 h of life from 50 % [2, 5, 7] to 30 %. We calculated that 103 newborns must be enrolled in each group to detect this difference as statistically significant with 80 % power at the 0.05 alpha level using the two-sided Pearson’s chi-square test.

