### Statistical analysis

The primary efficacy analysis will be conducted on an intention-to-treat basis. An as-treated analysis will also be implemented for secondary analyses if a large number of infants do not end up getting the treatment to which they were assigned. Clinical characteristics of infants in the “IN-REC-SUR-E” and “IN-SUR-E” groups will be described using mean values and standard deviation, median value and range, or rate and percentage. Univariate statistical analysis will be performed using the Student’s *t* test for parametric continuous variables, the Wilcoxon rank-sum test for non-parametric continuous variables, and Fisher’s exact test for categorical variables. A *p* value <0.05 will be considered statistically significant. Then, treatment arm and clinical characteristics which are most likely associated with the need for mechanical ventilation (gestational age, birth weight, antenatal steroids, CRIB score) will be included in a multiple logistic regression analysis to assess their independent role in predicting the clinical outcome. Effect estimates will be expressed as odds ratios (ORs) with maximum likelihood-based 95 % confidence limits. An interim analysis will be planned when 50 infants will be enrolled in each arm. The analysis will intend to compare treatment arms with respect to efficacy, safety, futility, assessment of difficulties with patient enrollment, and, if necessary, a sample size adjustment. In the interim analysis for safety the pre-specified stopping rules are: a mortality rate more than 40 %, a rate of severe IVH more than 30 % and a pneumothorax rate of more than 10 %. The interim-analysis will be performed by an independent statistician, blinded for the treatment allocation. The statistician will report to the independent Data and Safety Monitoring Board (DSMB). The DSMB will have unblinded access to all data and will discuss the results of the interim-analysis with the Steering Committee in a joint meeting. The Steering Committee will decide on the continuation of the trial and will report to the central Ethics Committee.

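### The interim compares the arms for efficacy at 48.5% of the data and informs continuation, but no efficacy threshold is given and the full 0.05 is kept for the end

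*Protocol article*

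**What the plan says.** All references are to the Protocol article.

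- **Timing** (Statistical analysis): "An interim analysis will be planned when 50 infants will be enrolled in each arm". With 206 infants in total, that is 100 of 206.
- **Purpose** (Statistical analysis): "The analysis will intend to compare treatment arms with respect to efficacy, safety, futility", together with enrolment difficulties and a possible change of sample size.
- **Consequence** (Statistical analysis): the monitoring board sees unblinded data and discusses the interim results with the Steering Committee, which decides whether the trial goes on.
- **Stopping rules** (Statistical analysis): numerical limits are given for mortality, severe intraventricular hemorrhage and pneumothorax. None is given for efficacy or futility.
- **Significance level** (Statistical analysis): a p "value <0.05 will be considered statistically significant". This follows the list of univariate tests, which names Fisher's exact test for categorical variables. No other level appears.
- **Sample size** (Sample size): "We calculated that 103 newborns must be enrolled in each group" to detect a fall in the primary outcome "during the first 72 h of life from 50 % [2, 5, 7] to 30" percent, "to detect this difference as statistically significant with 80 % power" "at the 0.05 alpha level using the two-sided Pearson’s chi-square test".

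**The concern.** An efficacy comparison that feeds a decision to continue gives the trial a second chance to declare success. If that chance has no threshold of its own, and the final test still uses the whole 0.05, the overall false-positive rate can exceed 5%. The excess depends on a number the article does not state.

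An early stop on a lenient threshold would also overstate the benefit. Suppose the trial's own 50% versus 30% were true and p<0.05 were used at 50 per arm. The chance of crossing in favour of the intervention would be about 46% (Fisher) or 55% (Pearson). The mean observed difference among those crossings would be about 28 or 27 points, against a true 20. A crossing at the interim is therefore a realistic event, and the rule for it needs to be fixed in advance.

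**Working it through.** **Inputs.** Rates 50% and 30%, two-sided alpha 0.05, power 80%, 103 per arm (Sample size); interim at 50 per arm, p<0.05, Fisher's exact test (Statistical analysis).

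**1. Does the sample size reserve any alpha for the interim?**

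- Uncorrected: n = [1.960·√(2·0.4·0.6) + 0.8416·√(0.25 + 0.21)]² / 0.20² = (1.3579 + 0.5708)² / 0.04 = 93.0.
- With continuity correction: n′ = (n/4)·[1 + √(1 + 4/(n·0.20))]² = 23.25 × (1 + 1.1023)² = 102.8, so 103.

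The stated 103 is reproduced exactly with the full two-sided 0.05 in one test. No alpha is set aside.

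**2. Information at the interim.** t = 100/206 = 0.485. The correlation between interim and final test statistics is √0.485 = 0.697.

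**3. Overall type I error, normal theory.** The error is 1 − P(|Z₁| < c₁, |Z₂| < c₂), with (Z₁, Z₂) bivariate normal and correlation 0.697.

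| Interim p | Final p | Overall two-sided error |
|---|---|---|
| 0.05 | 0.05 | 0.0836 |
| 0.01 | 0.05 | 0.055 |
| 0.005 | 0.05 | 0.052 |
| 0.001 | 0.05 | 0.0502 |
| 0.005 | 0.048 | 0.0500 |
| 0.0026 | 0.049 | 0.0499 |

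**4. The same with the actual tests.** Binomial data with 50 and then 103 per arm, equal rates in both arms, p<0.05 at both looks (400,000 simulated trials per rate):

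| Common rate | Fisher, one look | Fisher, two looks | Pearson, one look | Pearson, two looks |
|---|---|---|---|---|
| 30% | 3.6% | 5.7% | 5.1% | 8.4% |
| 40% | 3.9% | 6.0% | 5.3% | 8.8% |
| 50% | 3.3% | 5.8% | 4.5% | 8.5% |

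Exact enumeration agrees to within about 0.1 point. At a common rate of 45% it gives 6.0% (Fisher) and just under 8.9% (Pearson) for two looks. With p<0.001 at the interim and 0.05 at the end, Fisher's overall error stays at its single-look value.

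**5. Derivation of one boundary.** Lan-DeMets O'Brien-Fleming-type spending at 0.025 per side: 2·[1 − Φ(2.2414/0.697)] = 0.0013 per side, so two-sided p<0.0026 at the interim. The final critical value that brings the total to 0.05 is 1.967, or p<0.049. Putting the whole two-sided 0.05 into the same formula gives 0.0049. That is why the pair 0.005/0.048 also holds 5%, although it is not the usual Lan-DeMets figure.

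**6. Power at 50% versus 30%, 103 per arm (exact).**

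| Rule (interim/final) | Fisher | Pearson |
|---|---|---|
| Single look at 0.05 | 81.1% | 84.7% |
| 0.001 / 0.05 | 81.1% | 84.7% |
| 0.0026 / 0.049 | 80.8% | 84.4% |
| 0.005 / 0.048 | 80.3% | 84.2% |

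**The case against.** A reader might infer that the primary hypothesis is tested twice at 0.05, so that the 5% error rate is certainly lost and stands at 8.4% or more. The article does not support that reading. The p<0.05 sentence follows the univariate tests and comes before any mention of the interim. Nothing applies it to the interim look, and nothing says that the trial may stop for efficacy. A look that cannot lead to an efficacy stop or claim does not by itself inflate the error rate. The 8.4–8.9% range also belongs to Pearson's test, which appears only in the sample size; the analysis section names Fisher's test. All of this stands.

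It can also be said that this is a condensed article, and that boundaries commonly sit in an analysis plan or a monitoring charter that is not shown. That is fair for the details of alpha spending, and a boundary may well exist there. But the article goes beyond leaving the matter open. It fixes the look, names efficacy as one of its purposes, links it to a decision on continuation, lists stopping rules for safety alone and keeps an unadjusted 0.05. A boundary held elsewhere would still have to be reconciled with that text.

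The blinding of the interim statistician does not answer the point. The monitoring board is unblinded, and blinding does not remove multiplicity.

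**Conclusion.** The point holds conditionally. The article combines an efficacy comparison at 48.5% of the data with a continuation decision, no efficacy threshold, and a final level and sample size that use the full two-sided 0.05. The size of any inflation depends on the unstated threshold. It is nil if no efficacy stop or claim is possible, and negligible at p<0.001. If the only stated level were used at both looks, the overall error would be about 5.7–6.0% with Fisher's test, roughly 1 point above nominal at most, or 8.4–8.9% with Pearson's.

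These figures assume an unadjusted comparison of the primary outcome, looks at exactly 50 and 103 per arm, and common event rates of 30–50%. A sample size change based on unblinded data could add to the inflation; this was not quantified. The text should be corrected, but the omission does not show that the trial's error rate has been lost.

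**What to change.** Before any interim data are seen, add one of the following to the protocol or analysis plan.

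- **No efficacy stop.** State that the interim cannot lead to an efficacy stop or claim. The final test then keeps 0.05.
- **An efficacy boundary with a matching final level.** Any of these would serve:
  - Lan-DeMets O'Brien-Fleming-type spending at 0.025 per side: two-sided p<0.0026 at the interim and p<0.049 at the end;
  - the pair 0.005 and 0.048;
  - Haybittle-Peto: p<0.001 at the interim and 0.05 at the end (overall 0.0502).

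If the interim does not fall at exactly 100 of 206, the spending boundary should be recomputed at the actual fraction.

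The cost is wording only, with no added infants. The largest loss of power among these options is with 0.005/0.048: from 81.1% to 80.3% under Fisher's test, or 84.7% to 84.2% under Pearson's. Under Fisher's test this leaves little margin above the planned 80%, which favours one of the stricter interim thresholds.

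### The interim safety stopping rules are absolute event rates with no between-arm boundary and no stated denominator, so a clear excess of deaths or severe IVH need not trigger them

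*Protocol article*

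**What the plan says.** Everything on this point stands in the protocol article under Statistical analysis.

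- Timing: "An interim analysis will be planned when 50 infants will be enrolled in each arm".
- Purpose: "The analysis will intend to compare treatment arms with respect to efficacy, safety, futility", followed by enrollment difficulties and a possible sample size adjustment.
- Safety limits, all in percent. For death: "the pre-specified stopping rules are: a mortality rate more than 40". For bleeding in the brain: "a rate of severe IVH more than 30". For air leak: "a pneumothorax rate of more than 10".
- General test for categorical data: "Fisher’s exact test for categorical variables", with the threshold that a p "value <0.05 will be considered statistically significant".
- Governance: a statistician blinded to allocation performs the interim analysis. The DSMB sees all data unblinded and discusses the results with the Steering Committee, which decides whether the trial continues.

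No limit is expressed as a difference, ratio or test between arms. No limit says whether its denominator is one arm or both arms together.

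**The concern.** The stated purpose and the stated rules do not match. Harm from the recruitment maneuver would appear as an excess over IN-SUR-E, and the randomized control arm is there to measure it. A fixed rate without reference to that arm has two weaknesses.

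1. It can stay silent when the arms differ clearly, provided the higher arm is still at or below the limit.
2. It can be crossed when the arms do not differ, if the background rate in these infants is close to the limit.

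At stake is what the written rules contribute at the joint meeting. A limit that has not been crossed could be cited for continuing despite a marked excess of deaths. A crossed limit could be cited for stopping when the arms are alike.

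**Working it through.** **Inputs from the article.** Interim at 50 per arm (100 in total); limits of 40 %, 30 % and 10 %; Fisher's exact test; threshold 0.05. The article gives no operating characteristics for these limits, so there is no figure of its own to reproduce. It also gives no background rates for the three events; every true rate below is an assumption.

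**Step 1: turn the limits into counts.** Each limit is crossed only when the rate is exceeded.

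| Event | Limit | Per arm (n = 50) | Pooled (n = 100) |
|---|---|---|---|
| Death | > 40 % | 21 or more | 41 or more |
| Severe IVH | > 30 % | 16 or more | 31 or more |
| Pneumothorax | > 10 % | 6 or more | 11 or more |

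**Step 2: splits that trigger nothing.** Two-sided Fisher test on 50 vs 50. This step needs no assumed rate.

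| Reading | Event | Split | Fisher p |
|---|---|---|---|
| Per arm | Death | 20 vs 7 (40 % vs 14 %) | 0.006 |
| Per arm | Death | 14 vs 5 (28 % vs 10 %) | 0.040 |
| Per arm | Severe IVH | 15 vs 5 (30 % vs 10 %) | 0.023 |
| Pooled | Death | 26 vs 14 (total 40) | 0.024 |
| Pooled | Severe IVH | 20 vs 10 (total 30) | 0.049 |
| Pooled | Pneumothorax | 9 vs 1 (total 10) | 0.016 |

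Pneumothorax read per arm is the exception. The most extreme split that does not trigger is 5 vs 0, with p = 0.056, so that limit misses no excess that Fisher's test would call significant.

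**Step 3: chance of detecting a true excess.** Sum over all pairs (a, b) of Bin(a; 50, p_E) × Bin(b; 50, p_C), where p_E and p_C are the true rates in IN-REC-SUR-E and IN-SUR-E. The limit fires if either arm exceeds it. The test flags if the one-sided exact p for an excess in IN-REC-SUR-E is below 0.025. With equal arms this is the same as two-sided Fisher p < 0.05 in that direction.

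| Assumed true rates | Per-arm limit fires | Exact test flags | Test flags, limit silent |
|---|---|---|---|
| Death 30 % vs 10 % | 5 % | 64 % | 59 % |
| Death 35 % vs 15 % | 19 % | 57 % | 39 % |
| Death 40 % vs 20 % | 44 % | 52 % | 17 % |
| Severe IVH 25 % vs 5 % | 16 % | 75 % | 59 % |
| Severe IVH 30 % vs 10 % | 43 % | 64 % | 25 % |

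**Step 4: chance of crossing with no true difference.** For a common rate p, one arm crosses with probability q = P(Bin(50, p) ≥ k), either arm with 1 − (1 − q)², and the pooled rate with P(Bin(100, p) ≥ K), where k and K are the counts in step 1. For pneumothorax at 8 %: q = 0.208, so 1 − 0.792² = 0.373.

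| Event | Assumed common rate | Either arm | Pooled |
|---|---|---|---|
| Pneumothorax | 3 % | 0.7 % | < 0.1 % |
| Pneumothorax | 5 % | 7 % | 1 % |
| Pneumothorax | 6 % | 15 % | 4 % |
| Pneumothorax | 8 % | 37 % | 18 % |
| Severe IVH | 15 % | 0.4 % | < 0.1 % |
| Severe IVH | 25 % | 30 % | 10 % |
| Death | 25 % | 1.3 % | < 0.1 % |
| Death | 35 % | 34 % | 13 % |

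The either-arm column includes crossings in the control arm alone.

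**Step 5: false flags from a between-arm criterion.** At a common true rate, one-sided exact p < 0.025 with 50 per arm flags an excess in IN-REC-SUR-E with probability 0.4 % at 5 %, 0.9 % at 10 %, 1.2 % at 15 %, 1.4 % at 20 % and 1.5 % at 30 %.

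**The case against.** The strongest reply is that the limits are not the whole of safety monitoring. The same section says the arms will be compared on safety, names Fisher's test and gives the DSMB unblinded data. A board shown 20 vs 7 deaths would see the excess, and nothing makes the limits the only ground for stopping. This stands. A reader might infer that the trial has no between-arm safety comparison, or that such an excess would be overlooked. The article does not support either.

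A reader might also infer that crossing a limit ends the trial. It does not follow: the results go to a joint meeting and the Steering Committee decides.

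The figures for crossing with equal arms depend on rates the article does not give, and are small when the background is well below the limit. They are also lower on the pooled reading. The count splits in step 2 do not share this dependence, although 20 and 15 are the largest per-arm counts that do not trigger.

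Absolute ceilings are a legitimate design element, and replacing the pneumothorax limit with a test would weaken protection. At assumed rates of 15 % vs 5 %, the exact test flags 24 % of the time, while the IN-REC-SUR-E arm crosses the existing limit 78 % of the time. This stands, and it is why the fix leaves that limit alone.

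Finally, a condensed article may leave a comparative guideline or the denominator to the full protocol or the DSMB charter. That bears on missing detail. It bears less on rules that the article itself presents as pre-specified and that perform poorly on either reading.

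**Conclusion.** The point holds for the written rules. They are three absolute rates with no comparative boundary and no stated denominator, in an interim analysis whose stated purpose is to compare the arms. On either reading they stay silent for excesses of death and severe IVH that are significant by the article's own test. At assumed death rates of 30 % vs 10 %, the per-arm limit fires about 5 % of the time, against 64 % for an exact comparison.

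The second weakness, crossing a limit when the arms are equal, is conditional. It matters only if background rates lie near the limits: for pneumothorax, either arm / pooled is 7 % / 1 % at 5 % and 37 % / 18 % at 8 %.

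Unblinded DSMB review and a Steering Committee decision soften both consequences. This is an inexpensive improvement that should be made. It does not show that participants are left without safety oversight.

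**What to change.** In Statistical analysis, and in the DSMB charter if there is one:

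1. State that the three limits apply to each arm separately.
2. Keep all three absolute limits, including pneumothorax.
3. For death and for severe IVH, add a between-arm criterion: an excess in IN-REC-SUR-E over IN-SUR-E at one-sided exact p < 0.025 prompts the DSMB to consider recommending a stop.

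The change is wording only, and the comparison uses data already prepared for the interim analysis. The downside is a chance flag for harm of at most about 1.5 % per event for common rates up to 30 %. A flag leads to DSMB consideration, not to an automatic stop.

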### Blinding

The study will not be blinded, and the staff performing the study also will take subsequent care of the infants.

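### As written, the interim procedure allows comparative results to reach the Steering Committee of an unblinded trial at about 49% of planned enrolment; a closed DSMB session with a recommendation-only output should replace it.

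*Protocol article*

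**What the plan says.** All the interim rules stand in the Statistical analysis section of the protocol article.

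- **Timing:** "An interim analysis will be planned when 50 infants will be enrolled in each arm".
- **Content:** a comparison of the arms on efficacy, safety and futility, a look at enrolment difficulties and, "if necessary, a sample size adjustment".
- **Who analyses:** an independent statistician blinded to allocation, reporting to an independent DSMB.
- **Who is told:** the DSMB has unblinded access to all data and "will discuss the results of the interim-analysis with the Steering Committee in a joint meeting".
- **Who decides:** "The Steering Committee will decide on the continuation of the trial".

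Other sections bear on the consequences:

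- **Blinding:** the trial is unblinded and "the staff performing the study also will take subsequent care of the infants".
- **Primary outcome measure:** an infant also counts as a failure if not extubated within 30 min of surfactant, or if the nCPAP failure criteria are met after extubation.
- **Surfactant treatment:** extubation depends on satisfactory respiratory drive, and the choice of BiPAP or N-IMV to avoid re-intubation is left to the neonatologist on duty.

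**The concern.** A monitoring board is kept separate so that those who govern a trial can go on running it without knowing which arm is ahead. Here the route of disclosure is written into the plan. The board that sees unblinded data meets the deciding body, and the subject of the meeting is the results of a between-arm comparison. Nothing limits that discussion to a recommendation, to pooled data or to masked arms.

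This trial has little protection if a trend becomes known. Allocation is visible at the bedside, and two steps that feed the primary outcome leave room for judgement: whether respiratory drive is good enough to extubate in time, and which non-invasive support follows. Limitation (3) in the Discussion relies on clinicians using that support alike in both groups, which is the assumption that knowledge of a trend would weaken. Who is approached for enrolment could also shift. Such bias could not be removed at the analysis stage.

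A second matter sits in the same sentence of the plan. The sample-size adjustment is listed within an analysis that compares the arms, and is not tied to the pooled event rate.

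**Working it through.** **1. The plan's own sample size.** Inputs from the Sample size section: 50% versus 30%, two-sided alpha 0.05, power 80%.

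- Without continuity correction, with mean rate 0.40: n = [1.96·√(2·0.4·0.6) + 0.8416·√(0.5·0.5 + 0.3·0.7)]² / 0.2² = (1.358 + 0.571)² / 0.04 ≈ 93 per group.
- With continuity correction: (93/4)·[1 + √(1 + 4/(93·0.2))]² = 23.25·(2.102)² ≈ 102.8, so 103 per group.

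The stated 103 per group (206 in total) is reproduced and is not in question.

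**2. How far the trial has run at the interim.** 50 + 50 = 100 infants, and 100/206 = 48.5%. The remainder is 206 − 100 = 106, or 51.5%. This is an upper bound on the number enrolled after disclosure. The trigger is enrolment, and no recruitment pause is stated, so infants who enter during the 72 h follow-up, data cleaning, analysis and the meeting itself reduce it.

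**3. Do the stated safeguards close the route?**

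| Safeguard | Where | Does it cover the joint meeting? |
|---|---|---|
| Interim statistician blinded to allocation | Statistical analysis | No. Disclosure comes later, between the unblinded DSMB and the Steering Committee |
| Independent DSMB | Statistical analysis | In part. It receives the report first, but is then to discuss the results with the deciding body |
| No early presentation of data that break the blind | Dissemination policy | No. It governs presentations and publications |

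**4. What effect-driven resizing could cost.** This is separate from who attends the meeting. Assumptions: first stage n₁ = 50 per arm, planned second stage 53 per arm, normal approximation, and an ordinary final test at one-sided 0.025 (half of the two-sided 0.05). Given the interim statistic z₁ and a second stage of n₂ per arm, the chance of a false positive is

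1 − Φ( [1.96·√(n₁ + n₂) − z₁·√n₁] / √n₂ ).

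The worst case takes the n₂ that maximises this at every z₁ and averages over z₁ under no effect. With n₂ fixed at 53 it returns 0.025, as it should.

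| Second stage allowed | Worst-case one-sided error | Ratio to 0.025 |
|---|---|---|
| Increases only, total up to 309 (1.5 times) | 0.029 | 1.16 |
| Increases only, total up to 412 (2 times) | 0.031 | 1.24 |
| Increases only, unlimited | 0.043 | 1.72 |
| Any size from 0 to 156 per arm | 0.050 | 2.0 |
| Any size from 0 to unlimited | 0.062 | 2.5 |

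The last row agrees with the closed form 0.025 + exp(−1.96²/2)/4 = 0.025 + 0.1465/4 = 0.0616. It needs a second stage that may be of any size, including stopping at once with success whenever the interim z exceeds 1.96. The plan describes nothing of that kind.

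**The case against.** The strongest reply is that the wording permits disclosure without requiring it. The statistician is blinded, so results labelled A and B would fit the text. The membership of the Steering Committee is not given, and nothing says that results travel on to bedside staff. A reader might infer that the people treating the infants will learn which arm is ahead, or that the DSMB's independence is defeated. The document supports neither: it provides an independent board that receives the report directly. What stands is narrower. No text limits what is discussed, and the body that decides on continuation takes part. Because the article states this as a rule, it cannot be set aside as detail left to a fuller document.

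A second reply is that the bias route is limited. The nCPAP failure criteria rest on FiO₂, blood gases and apnea counts, so the decision to re-intubate does not alone determine failure. Staff also know each allocation already, so interim knowledge would add to an existing risk. Both points are fair and lower the likely size of the bias. They do not cover the judgement about respiratory drive within the 30 min window, or the free choice of BiPAP or N-IMV.

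A third reply is that error inflation has nothing to do with the joint meeting. That is correct. Effect-driven resizing followed by an ordinary test inflates the error whoever does it, including the DSMB alone. The plan does not say that the adjustment uses the observed effect, or that the Steering Committee sets the size.

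**Conclusion.** The point holds as a fault in a stated procedure and should be fixed. As written, the plan allows comparative interim results to reach the body governing an unblinded trial at 48.5% of planned enrolment, with up to 106 infants still to come. Their primary outcome depends partly on judgement.

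The conclusion rests on reading the discussed results as the between-arm comparison that the same section describes, and on treating the Steering Committee as the governing body because it decides on continuation. Any effect on later care also requires that knowledge reach or influence the centres. The document does not show this, and the resulting bias is not quantified.

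A reader might infer that the joint meeting raises the one-sided error from 0.025 to 0.062, about 2.5-fold. The document does not support that. The figure needs an unrestricted second stage, and it would measure effect-driven resizing rather than disclosure. With increases only, the corresponding ceilings are 0.029 to 0.043, and they apply only if the size is driven by the observed effect and the final test is left unadjusted.

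**What to change.** 1. Replace the joint discussion of results by a closed DSMB session. The DSMB then sends the Steering Committee a written recommendation (continue, modify or stop), without arm-level results unless it recommends stopping. An open session on recruitment and data quality, without comparative data, can remain.
2. State that any sample-size adjustment will use only the pooled, blinded event rate.

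The cost is a change of wording in the protocol and the DSMB charter, with no extra infants or data. The Steering Committee keeps the formal decision and gives up sight of comparative interim data. The change has to be made before the interim analysis, because disclosure cannot be undone.
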